# Research Plan and Methods

## Trial design

The planned study will be a multi-centre, randomized controlled, parallel-group trial with 1:1 allocation ratio of a CDM model intervention versus usual care in CLD patients. The study will follow CONSORT guidelines, where relevant, for the design, conduct, and analysis of RCTs.

## Study duration

At each site, recruitment will occur for 12-18 months, and then the trial will continue until the last participant recruited has had 24 months of CDM (total 3-year study duration).

## Number of Participants

The aim is to enrol 150 patients into the study but sites will be allowed to recruit until a maximum of 200 patients are enrolled.

## Treatment Assignment

Participants will be randomized in a 1:1 ratio to receive usual care or the intervention from Day 1 through to study end.

## Participant Population

This study will be conducted at 4 sites in Australia at which the CDM model of caring for patients with cirrhosis has not been instigated. Participants will be from inpatient admissions where patients have come into hospital with a symptom of decompensation.

## Participant Inclusion Criteria

1. Cirrhosis of the liver
2. Admitted to hospital with an episode of decompensation including one of:
   - Ascites
   - Encephalopathy
   - Variceal bleed
   - Spontaneous bacterial peritonitis
   - Hepatorenal syndrome
3. Patients who have attended an outpatient liver clinic with a hospital admission in the last 6 months and a Child Pugh B or C score
4. Able to comprehend and willing to sign an Informed Consent Form (ICF) (West Haven Criteria = 0 or 1)
5. Patients with mild cognitive impairment, at PI’s discretion
6. Age ≥18 years

## Participant Exclusion Criteria

1. Currently involved in a multidisciplinary heart failure program
2. Diagnosis of active hepatocellular carcinoma (HCC)
3. Active management by Palliative Care Services or expected survival of < 3 months
4. Currently on the liver transplant waiting list

## Consent of potential participants

Consulting clinicians, or the study PI, will verbally consent patients to allow the study team to access their medical records to determine eligibility into the study. Consent will be recorded either electronically or in hardcopy patient notes. Upon consent, study nurses will review case notes to determine potential inclusion. The treating team can also let the trial nurse know if there is a potential participant under their care. If Hepatic Encephalopathy is the admission criteria or a present as a concurrent condition on admission the investigator needs to provide an assessment for Encephalopathy using a standard assessment – the West Haven Criteria. A score of 0 or 1 documented in the patient notes by the treating team or trial investigator means that the patient can be approached for consent. Participants who meet inclusion criteria and do not have exclusion criteria will be approached by the site investigator or site nurse. Investigators or nurses can obtain consent for the trial. Potential participants will be inpatients in hospital, or approached after an outpatient appointment, and will receive the information sheet with an explanation about the trial by investigators or nurses and be given opportunity to discuss the trial with family members or to consider the trial. Consent will occur before the patient is discharged from the hospital and can be obtained by investigators or trial nurses. Both consent for the ALFIE trial as well as specific consent for access to MBS and PBS data will be sought. The intervention will commence prior to discharge from hospital.

Patients with mild cognitive impairment may be approached and consented for the study at the site PI’s discretion. If required, a third-party person responsible PISCF can be provided by the PI or study coordinator to the person responsible for the potential participant to obtain informed consent.

The patient will be reassured verbally that their medical care in hospital will not be affected by their participation or non-participation in the trial.

*Recruitment during the COVID-19 Pandemic*

Due to the COVID-19 pandemic and the need to maintain social distance from all potential participants, recruitment methods will be altered to ensure patient and staff safety.

Potential participants admitted to hospital may be approached by the site CLD nurse, or if restrictions are in place, the treating doctor or site PI can approach the patient about the study and undertake consenting as per current protocol.

Participants that would usually be approached during an outpatient appointment may now be contacted about the study via a phone call from the CLD nurse. The nurse will explain the study to the patient as per usual process. If the patient is agreeable, then the CLD nurse will email the patient using the ALFIE Email Consent Template. The email, with site PI cc’d, will contain details about the trial, and will have the ALFIE PISCF, the ALFIE MBS/PBS Consent Form and baseline electronic surveys attached. The patient will be asked to reply to both CLD nurse and site PI confirming that they have read and understood the PISCF and convey that they consent to taking part in the trial. Consenting participants will need to also convey consent to MBS and PBS data access, as well as send back the completed electronic surveys. The CLD nurse will then print the email consent and file into site folders and continue to randomisation. Hardcopies of the consent forms will be sent to each consenting patient with a reply paid envelope as Services Australia requires the hardcopy consent to release MBS and PBS data.

# Intervention and Implementation

The term ‘intervention’ refers to the Chronic Disease Management model applied to the care of the patient with cirrhosis of the liver. The intervention starts after randomisation and will continue until the end of the study which is 24 months after the first randomised patient.

Randomisation signals the start of the treatment period. Every Participant will have at 24 months of intervention.

## The Chronic Disease Management Model:

- A ‘patient identification card’ (Appendix B) for patients to use to indicate their involvement in liver disease case management to use in emergency departments, GPs, or other health services.
- An initial home visit(s) for assessment and education within 7 days of discharge from hospital or consent and includes education for:
  - Medication adherence
  - Cirrhosis education
  - Assessment for complications of liver disease not previously diagnosed
  - Assessment of any barriers to self-management
- Development of a Care Plan with the Hepatologist and the patient
- Weekly phone contact for the first 3 months of intervention for ongoing assessment and education, then 3 monthly to 12 months, then 6 monthly if appropriate.
- Early Hepatologist review post hospital discharge (within 4 weeks)
- Patient reminders prior to appointments
- Case management of symptoms of decompensation such as ascites, hepatic encephalopathy and SBP which are protocol led
- Referral pathways for alcoholic liver disease
- General Practitioner communication including entry into the study, discharge summaries, care plans, changes to medications, and discharge from the service.
- A direct telephone number provides rapid access to care for patients requiring symptom assessment and management
- Case conference reviews during hepatology outpatient appointments attended by the patient and the CLD nurse

**Decision making support is available to the CLD nurse via:**

- Evidence based protocols for all major complications of cirrhosis provided to all CLD nurses
- Protocol driven CLD and disease specific checklist

**Self-management support will be given to the patient via:**

- - Patient information booklet on cirrhosis containing medication list, weights, action plans, appointment details, contact numbers
  - Enhanced patient and carer education during contacts with the CLD nurses concerning diet, medications, need for investigations
  - Self-monitoring of weight for patients with ascites using digital scales
  - Medication blister packs where applicable to improve adherence

**Clinical information systems:**

- Individual patient data sheets with problem lists, medication lists and weight charts provided by CLD nurses to hepatologists during outpatient reviews.
- Recall and reminder system for CLD nurses using Microsoft office.

## Role of CLD nurse

Patients in the Intervention Group (Case Management (CM) group) will have a CLD nurse home assessment within a week of randomization. This assessment, together with input from the specialist will produce a protocol driven, but individualized care plan which will be distributed by the CLD nurse to the patient, gastroenterologist and GP and be placed in the patient’s hospital record. The CLD nurse will then facilitate implementation of the plan by promptly organizing required investigations and assisting the patient to attend and coordinate their own medical and allied health visits, and provide written ± telephone reminders prior to each liver-related appointment. Patients in the CM group will be reviewed by CLD nurses through weekly telephone calls. Patient deterioration will be promptly reported to the patient’s specialist, to enable early intervention and help avoid emergency admissions. Patients who achieve stable clinical states by three months may subsequently receive less intense monitoring with telephone contact as designated by the treating team, which can be escalated as required. CLD nurses will support the patient and carer in their communication with the health care team and will educate all those involved in the care plan about the model of care and the central role of the patient. CLD nurses will be accessible to patients, carers and team members via mobile phone during business hours. For after-hours medical advice the CLD patients will access on call teams for each site via usual care pathways.

## Role of Gastroenterologist/Hepatologist

Gastroenterologists usually involved in the inpatient and outpatient care of CLD patients at each site will continue to be involved with both intervention and usual care patients. However, the CLD nurse will improve the continuity of care with gastroenterologists for intervention patients by facilitating optimal patient contact with their usual gastroenterologist during the trial. The gastroenterologists involved with intervention patients at each site will be supported by the dedicated Hepatology chief investigator at each site. The gastroenterologist will be involved in formulation of the initial care plan and subsequent modification when appropriate. The gastroenterologist will be accessible to the CLD nurse for non-contact patient reviews when concerns arise about patient deterioration. The gastroenterologist will receive enhanced support during non-contact and direct contact patient reviews from the CLD nurse who will provide care plan updates which include: medically defined problem lists, medication lists, relevant clinical data (i.e. MELD scores and weight charts), key investigation results and patient defined problem lists including personal and lifestyle goals.

## Role of General Practitioner

Following recruitment, the CLD nurse will involve the intervention patient’s GP at an early stage and will communicate hospital information as well as care plans from the intervention. GP communication will occur (using a method chosen by the patient’s GP) at hospital admission or discharge, or any major change to the patient’s care plan.

## Control/usual care group

Control/usual care patients will continue hospital and out of hospital management via usual care processes. To prevent contamination of usual care patients by the intervention, usual care patients will have no contact with CLD nurses until a final end of study interview. Usual care patients will be mailed surveys at baseline, 3 months, 6 months, and then 6-monthly until the end of the trial (24 months after the first patient randomised). At the end of the trial, control group participants are invited for a face-to-face review to complete the surveys, are given the Cirrhosis Booklet and offered an education session.

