## Outpatient review by Specialist Gastroenterologist/Hepatologist

Review by a specialist must be scheduled within 1 month (4 weeks) of discharge from hospital for all patients in the intervention group. The nurse must attend this appointment with the patient. In preparation for the outpatient appointment the following should be updated:

- - Medication list
  - Care Plan
  - Ensure screening and surveillance requirements are up to date (or booked)

At this appointment the specialist will discuss the care plan with the nurse and the patient and sign off on the care plan.

## Month 3, Month 6, Month 12, Month 18

Patients in the intervention group have their Child Pugh and Meld scores completed at 3, 6, 12, 18 months and at end of trial (Appendix N). Collect the information from the most recent bloods taken as part of usual care, the patient will not be required to have a blood test taken just for this score to be done.

Surveys are due for both groups at this time. For intervention patients this should ideally be scheduled at the same time the specialist outpatient appointment is scheduled to enable accurate determination of the Child Pugh and MELD score. Ensure the contact log is up to date. Patients will be provided the option of receiving the surveys via standard post or electronically, via email, at consent.

Record hospital and liver-related outpatient admissions/attendances/non attendances at the month 12 visit.

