## End of Study

Patients will have an end of study visit at withdrawal, when listed on the transplant waiting list, or at the end of the study (24 months after the randomisation of the first patient).

Both groups will have the following collected:

- Cirrhosis Knowledge Assessment Questionnaire
- Ask 12
- CLDQ
- EQ-5L-5D
- PIH Scale
- Patient Satisfaction Questionnaire
- Resource use questionnaire
- MBS and PBS information (to be collected centrally by the coordinating site) if the patient signed the consent form at the beginning of the trial.

Please remind the participant that a member of the study coordinator team may be in contact via telephone to ask a few questions about their experiences but they can refuse to participate if they wish. Thirty two patients will be consecutively recruited (8 patients per site, 4 patients from each study arm) for the telephone interviews.

The following will also be completed/updated at end of study in both groups:

- Hospital admissions log
- Outpatient attendance log
- Concomitant medications
- Comorbidities list
- Child Pugh & MELD score
- HCC assessment
- Ascites and HE assessment
- Osteoporosis assessment
- Alcohol assessment
- Variceal assessment
- Nutrition assessment

It is preferable that the information is collected face-to-face as the control group patients can have some education about their liver disease if they wish. Ensure they receive the Cirrhosis Booklet.

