## Statistical methods

All analyses will be performed according to an intention-to-treat protocol. Differences between groups for hospitalization rates, quality indicators, satisfaction rates and self-management scores will be assessed using negative binomial regression, which is appropriate for count data with evidence of over-dispersion. All models will allow adjustment for baseline values and other co-variates. Suitable transformations will be applied in the case of non-normally distributed data.

For the economic analysis mean costs between the intervention and control groups will be compared and incremental cost effectiveness ratios presented with confidence intervals. Cost effectiveness acceptability curves for varying threshold values of cost effectiveness will also be presented ([46](#_ENREF_46)). An assessment of the sensitivity of the results obtained to variation in measured resource use, effectiveness and/or unit costs will be undertaken using appropriate one-way and multi-way sensitivity analysis ([47](#_ENREF_47)). Differences between groups in quality of life scores will be assessed using mixed effects regression to account for the repeated measures (every 3 months) and subsequent within-Participant correlation. Survival analysis will be performed using Cox regression with results presented as Kaplan-Meir survival curves.

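### By default the survey setting differs by arm at Months 3 to 18 and changes in controls at end of study, and how each survey was completed is not recorded

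*Protocol*

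**What the plan says.** **Control arm.** Under Control/usual care group, "Usual care patients will be mailed surveys at baseline, 3 months, 6 months, and then 6-monthly until the end of the trial". Under Baseline – all patients, staff are to tell patients randomised to usual care that later surveys will come by post. The same control section says that "usual care patients will have no contact with CLD nurses until a final end of study interview", and then: "At the end of the trial, control group participants are invited for a face-to-face review to complete the surveys, are given the Cirrhosis Booklet". An education session is also offered there.

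**Intervention arm.** Under Month 3, Month 6, Month 12, Month 18, the protocol says that surveys are due in both arms and adds: "For intervention patients this should ideally be scheduled at the same time the specialist outpatient appointment is scheduled". The reason given is accurate Child Pugh and MELD scoring. The intervention activity schedule marks face-to-face contact and a hepatologist outpatient visit at Months 3, 6, 12, 18 and 24. The control schedule has neither row. The Chronic Disease Management Model section has the CLD nurse attend the outpatient case conferences.

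**Both arms.** The Month 3 to 18 section lets patients choose post or email at consent, naming no arm. Data Monitoring has the CLD nurse send and receive the emailed surveys, again naming no arm. The baseline and end-of-study checklists (Appendices A and Q) list the surveys as completed by the patient. At End of Study, "It is preferable that the information is collected face-to-face as the control group patients can have some education about their liver disease if they wish".

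**Analysis.** "Differences between groups in quality of life scores will be assessed using mixed effects regression to account for the repeated measures (every 3 months"), according to Statistical methods. Self-management scores are assigned to negative binomial regression.

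**The concern.** Patient-reported scores can depend on where and with whom they are given. Under the default instructions a control answers at home. An intervention patient may answer at a clinic visit attended by the nurse who coaches that patient on adherence, self-management and knowledge of cirrhosis. That nurse also has a use for the answers: the home visit form (Appendix I) and the medication form (Appendix P) both turn ASK-12 responses into care-plan actions. Blinded outcome assessors do not help here, because the patient is the rater.

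If setting shifts the scores, part of a difference between arms at Months 3 to 18 could come from setting rather than from the intervention. A change in controls between Month 18 and end of study could also come from the change in setting. The final control meeting combines the surveys with the booklet and education, and one of the surveys tests knowledge of cirrhosis. At stake are the stated secondary objectives on quality of life and QALYs, self-management and knowledge, and medication adherence.

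**Working it through.** The protocol states no figure for a mode effect, so there is nothing to reproduce. The check has two parts.

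**1. Setting by arm and time point**

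Survey months come from the two activity schedules. Elsewhere the protocol differs: Statistical methods gives a 3-monthly interval, and the cost-effectiveness section lists interim EQ-5D-5L and CLDQ for the intervention group only.

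| Time point | Control | Intervention |
|---|---|---|
| Baseline | Collected before randomisation (the control section says mailed) | Collected before randomisation |
| Months 3, 6, 12, 18 | Mailed; email possible | Ideally scheduled with the specialist visit; post or email possible |
| Month 24 / end of study | Invited to a face-to-face review with the CLD nurse | Face-to-face preferred |

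The default differs at 4 of 5 post-baseline points (4/5 = 0.8). It is nominally aligned at the fifth, and that is where the control arm's own setting changes. None of the forms shown has a field for how a survey was completed.

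**2. Size, as an illustration**

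Inputs:
- m = shift in score from in-person rather than postal or emailed completion, in SD units. Assumed 0.1 to 0.3.
- f = share of intervention surveys at Months 3 to 18 done in person. Unknown, so taken as 0, 0.5 and 1.
- Controls are taken as all by post or email at Months 3 to 18, and the arms as aligned at Month 24.
- n per arm = 75 (Randomization, stratification, blinding), or 75 × 0.8 = 60 after the 20% attrition in the sample size section.

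Formulas:
- Bias at one visit, Months 3 to 18 = f × m.
- Bias averaged over five equally weighted visits = (4 × f × m + 0)/5 = 0.8 × f × m.
- Two-sided false-positive rate at one visit, with no true effect = P(|Z + f × m/√(2/n)| > 1.96).

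With n = 60, √(2/60) = 0.183. With n = 75, √(2/75) = 0.163.

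| f | m (SD) | Bias, one visit | Averaged bias | False positive, n = 60 | False positive, n = 75 |
|---|---|---|---|---|---|
| 1 | 0.1 | 0.10 | 0.08 | 8.5% | 9.4% |
| 1 | 0.2 | 0.20 | 0.16 | 19.5% | 23.2% |
| 1 | 0.3 | 0.30 | 0.24 | 37.6% | 45.1% |
| 0.5 | 0.1 | 0.05 | 0.04 | 5.9% | 6.1% |
| 0.5 | 0.2 | 0.10 | 0.08 | 8.5% | 9.4% |
| 0.5 | 0.3 | 0.15 | 0.12 | 13.0% | 15.1% |
| 0 | any | 0 | 0 | 5.0% | 5.0% |

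Equal weighting is a simplification. A comparison at one of Months 3 to 18 carries f × m, and one at Month 24 carries none if the arms are aligned there.

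**The case against.** A reader might infer that intervention surveys are tied to in-person visits, so that mode and arm are the same thing at Months 3 to 18. The protocol does not say so. It states an ideal, about scheduling, justified by Child Pugh and MELD scoring, and the same section offers post or email without naming an arm. In the schedule, surveys and face-to-face contact are separate rows, so marks in the same month do not show how a survey was completed. The surveys are self-completed, so what differs is setting and return route; nothing shows interviewer administration.

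A reader might also take 0.8 × m as the expected bias. That fixes f at 1, which the documents do not support. Nor do they give any return rates, so a lower return by post is only an expectation. The mixed model is specified for quality of life only and should not be blamed for every survey outcome. End of study is the point at which the arms are meant to be alike, and the control section lists the surveys before the booklet. Finally, keeping controls away from the CLD nurses has a stated reason, the prevention of contamination, and different contact patterns are inherent in a trial of care delivery.

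All of this limits the claim but does not remove it. The instruction favouring the specialist visit names one arm only, the mailing instruction names the other, and no common mode is set. Word order is not a rule that surveys come first, and End of Study gives education as a reason for preferring a face-to-face meeting. Preventing contamination does not require different survey routes.

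**Conclusion.** The point holds in a limited form. Survey setting overlaps with arm by default at four of the five post-baseline points and changes in controls at the fifth. Because mode is not recorded, the analysis cannot adjust for it. The exposed outcomes are CLDQ, EQ-5D-5L and the QALYs built on them, PIH, cirrhosis knowledge and ASK-12. The primary outcome, unplanned liver-related admissions, is not a survey measure and is untouched.

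The size cannot be known from the protocol. It depends on f, which local practice and patient choice will set, and on m, which is assumed. It disappears only if no intervention patient completes surveys in the setting that the protocol calls ideal. The change is worth making because the remedy is cheap and cannot be applied after the data are collected.

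**What to change.** Revise Control/usual care group, Baseline – all patients, Month 3 to Month 18, End of Study and Data Monitoring so that they agree on the following:

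- At every post-baseline time point, including end of study, both arms self-complete the surveys by the same patient-chosen route (post or email), without the CLD nurse.
- Surveys are returned to the coordinating centre, with the same window and the same reminders in both arms. This also removes the conflict between keeping controls away from CLD nurses and routing emailed surveys through them.
- The mode and date of completion are recorded for each survey.
- The specialist-appointment scheduling applies to Child Pugh and MELD only.
- Controls receive the booklet and education only after their end-of-study surveys are completed.

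The cost is protocol wording, postage, central reminders and one added data field. The downside is possibly somewhat fewer returns in the intervention arm than with completion in clinic.

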## Recruitment and consent process

Patients: Informed consent for the interviews was obtained during consent into the study, but patients will be provided the option of being contacted or not. Potential participants will be invited to take part in the telephone interview by their CLD nurse during their end of study visit and will obtain consent for the designated interviewer from FMC to contact them. The CLD nurse will inform the patient that the interview will take approximately 20 minutes and will involve briefly talking about their experience being involved in the ALFIE trial. If the patient consents, the CLD nurse will pass on their name and contact details to the designated interviewer. The designated interviewer from FMC will then contact the patient to conduct the interview. The participant will be advised that they can change their mind and cancel the interview if they wish.

Staff: The designated interviewer from FMC will email staff participants with the information sheet and request a convenient time to conduct the interview. As all interviews will be conducted over the phone, the staff participant will respond with email consent if they are interested in participating and will have seven days to consider participation. Upon consent, staff participants will be provided the interview questions 1 day prior to the interview, to ensure that they have sufficient time to consider their answers. The participant will be advised that they can change their mind and cancel the interview if they wish.

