## Appendix V – ALFIE Interview Questions for Patients

Introduction

Hi, I’m XX. Thank you for your time today. I am not a member of the ALFIE trial but have been asked to assist the research team with conducting these phone interviews. The aim of this interview is to find out about your experience being part of the ALFIE trial.

Questions

1. Tell me about your experience of having your liver disease managed at <your hospital>.
2. Was anyone involved in your care besides doctors?
3. Did you have a special liver nurse in charge of your care?
4. If yes, could you tell us about your experience receiving care from this liver nurse?
5. Did you feel supported during your treatment?
6. Did you receive any education about your liver disease?
7. Did you learn about self-management for the complications of your liver disease?
8. Do you feel confident about receiving appropriate care for your liver disease?
9. What were some of the good things about the care you received for your liver disease?
10. Do you have any complaints about the care received?
11. Is there anything that would have made the care you received for your liver disease any better?
12. Do you have any other feedback about the care you received by the liver department at <your hospital>?

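### Controls receive the booklet and an offer of education before the telephone interview, and the interview questions on education and self-management do not exclude that exit visit

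*Protocol*

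**What the plan says.** Four parts of the protocol bear on the order of events for a control patient.

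- **Control/usual care group.** To avoid contamination, "usual care patients will have no contact with CLD nurses until a final end of study interview". At the end of the trial, controls are invited to a face-to-face review to complete the surveys, and they "are given the Cirrhosis Booklet and offered an education session".
- **End of Study.** In-person collection is preferred because "the control group patients can have some education about their liver disease if they wish". Staff are told: "Ensure they receive the Cirrhosis Booklet". They also remind participants that "a member of the study coordinator team may be in contact via telephone to ask a few questions about their experiences".
- **Recruitment and consent process (qualitative analysis).** Patients are "invited to take part in the telephone interview by their CLD nurse during their end of study visit". If the patient agrees, the nurse passes on the contact details, and "The designated interviewer from FMC will then contact the patient to conduct the interview".
- **Appendix V.** Question 6 reads "Did you receive any education about your liver disease". Question 7 asks whether the patient learned about self-management of complications. Neither names a period.

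The qualitative section also sets 8 interviews per site, 4 from each arm, and blinds the interviewer to randomisation group and hospital. Its first secondary aim covers the patient's experience as regards satisfaction, education and support for self-management.

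**The concern.** A cirrhosis information booklet and enhanced education are components of the intervention, listed under self-management support. The protocol keeps controls away from the liver nurses during follow-up precisely so that usual care stays usual. At the closing visit it gives controls a booklet and offers teaching, which is a reasonable courtesy, but one data collection is still to come. That data collection asks about education and self-management.

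A control who was taught at the exit visit and is telephoned afterwards can truthfully answer yes to question 6, and possibly to question 7, even if usual care provided neither. What is at stake is whether the control accounts describe usual care or a mixture of usual care and a trial procedure.

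**Working it through.** No formula for power or error rate applies. The check is on the order of procedures, the number of people exposed and the questions affected.

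**1. The plan's own figure.** The Participant Population section gives 4 sites. The qualitative section gives 8 patients per site, 4 per arm.
- Total interviewees: 4 × 8 = 32, which agrees with the stated thirty-two.
- Controls among them: 4 × 4 = 16, which is 16/32 = one half.

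**2. Order of events for a control.**
- End-of-study visit: surveys, booklet given, education offered (Control/usual care group; End of Study).
- At the same visit: the liver nurse invites the patient to the interview (Recruitment and consent process).
- After the visit: the interviewer makes contact and conducts the interview (same section).

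The interview therefore follows the booklet and the offer of education. No section provides for the reverse order.

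**3. Number exposed.**
- Booklet: given as routine, so up to 16 of 16 interviewed controls.
- Education session: offered, and taken only if the patient wishes. The protocol gives no uptake figure, so the range is 0 to 16 of 16.

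**4. Questions affected, out of the 12 in Appendix V.**
- Question 6 (any education): directly affected, since either the booklet or the session supports a yes.
- Question 7 (learned self-management): affected if the session or booklet covered it.
- Question 2 (anyone besides doctors involved in care): weakly affected. Usual care may include allied health contacts, so a control may answer yes anyway.
- Question 3 (a special liver nurse in charge of care): hardly affected. One closing visit does not put a nurse in charge of care.

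The firm cases are thus 2 questions, 6 and 7.

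**5. Can the two periods be separated later?** The interviewer does not know the arm, so cannot tell which patients met education only at exit. No question in the script asks when education took place. Separation depends on the patient volunteering it.

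**The case against.** The strongest reply is that there is no comparison to damage. The qualitative review is described as inductive and descriptive. Its primary aim is to understand how the trial was conducted, and its first secondary aim names no contrast between arms. The analysis is a coding of text into themes, with no count of yes and no answers and no test. The interviews are open-ended conversations, and question 1 opens with the patient's care at the hospital as a whole. A patient may well say that the teaching came in one session at the end, and this could be coded.

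Most of this stands, and it limits the point. A reader might infer that a planned comparison between arms is contaminated or erased; the protocol states no such comparison. A reader might also infer that every control receives a nurse-led session. The session is optional, and the protocol does not say who delivers it; delivery by the nurse is only an inference from the nurse's presence at the visit.

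A third tempting inference is that the satisfaction, knowledge and self-management surveys are affected as well. The Control/usual care group section lists the surveys ahead of the booklet and education, and no section puts education before them.

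The reply does not remove the ordering itself. Sampling 4 patients per arm per site and blinding the interviewer to arm suggest that accounts from both arms are of interest. Even on a purely descriptive reading, a control's account of education should not include a trial-exit procedure unnoticed. An open conversation may reveal the timing, but nothing in the script ensures it.

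**Conclusion.** The point holds in a limited form. As written, the accounts of education and self-management from up to 16 of 32 interviewees may mix usual care with what the trial itself supplied on exit. The firm effect is on questions 6 and 7 and so on the education and self-management themes of one secondary aim of the qualitative review.

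The upper figure of 16 assumes that the interview quota is met at all four sites and that every interviewed control has received the booklet before the call. How many will also have had the session cannot be said. The direction is towards control accounts that show more education than usual care provided. The primary outcome, unplanned liver-related admissions, and the survey outcomes are not affected. The change is worth making because it is nearly free beforehand, while the two sources of education cannot be reliably separated once the interviews are done.

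**What to change.** **Preferred:** word questions 6 and 7 of Appendix V, and question 2 for consistency, to ask about care received before the end-of-study visit. The same wording serves both arms, so it does not reveal allocation to the interviewer, and it delays no one's education. The cost is a few words in the script.

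**Alternative:** for controls who agree to be interviewed, give the booklet and education after the call, and say so in Control/usual care group, End of Study, and Recruitment and consent process. The cost is a delay for up to 16 patients equal to the gap between visit and call. The protocol does not state this gap; a few days is assumed here. This option does nothing for question 2, because the visit with the nurse still precedes the call.
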